### Baseline variables (patient characteristics, complications, surgical characteristics)

- Will be described using simple descriptive statistics using means/median and standard

deviations/interquartile range for the continuous variables, whereas categorical variables are expressed as absolute and relative frequencies. Continuous variables will be tested for normality using the Kolmogorov-Smirnov test and by computing histograms and consequently expressed as mean  $\pm$  standard deviation (SD) when normally distributed, and as median  $\pm$  interquartile range (IQR) when skewed.

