**Secondary Objective(s):**

- Hearing outcomes
- Health-related quality of life
- Describing localization and disease extension using the STAMCO classification
- Health economic cost analysis
- Comparing any differences in patient and surgical characteristics

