#### 6.1.2 Secondary study parameters/endpoints

- **Baseline characteristics:**
  - Patient demographics (age (as collected by birthyear), gender), date of first presentation at the outpatient clinic, date of surgery, operated side (right/left), applied antibiotic treatment within in 2 weeks prior to surgery.
  - Co-morbidities and lifestyle factors: smoking, obesity, asthma, diabetes, COPD, allergies, rhinosinusitis.
  - Amount and type of all previous ear surgeries which are not mentioned in the exclusion criteria.
- **Hearing outcome:**
  - As measured by audiometric testing (pure-tone average thresholds (PTA) as calculated over 0.5, 1, 2 and 4 kHz for the air-conduction (AC) and bone-conduction (BC) and speech audiometry. This will be measured before the surgery, and at 6-18 weeks and around 1 year after surgery. The pre-operative audiogram should not have been measured more than 6 months prior to surgery.

- **Surgical characteristics:**

- A short 'standard' surgical report/template written by the participating otologists per center will be collected and used in the scientific publication to demonstrate any potential differences in surgical technique. This **does not** include patient information.
- STAMCO-classification: Localization and extension of the cholesteatoma, presence of preoperative complication status and the ossicular chain status before/at the time of removal of the cholesteatoma will be recorded. Any differences in outcomes in STAMCO classifications between the two randomized groups will be evaluated and described.

**Figure 2:** Localization, disease extension and complications as described by the STAMCO classification (18, ten Tije et al.)

[figure not shown]

- Material used for obliteration (Bonalive®, bonedust, hydroxyapatite, cartilage, muscle) as registered in the surgical report.

- Ossicular chain reconstruction (OCR); performed (yes/no), if yes, the used material and type of reconstruction (PORP, TORP, use of incus interposition, type 3 tympanoplasty) will also be reported.
- Surgical personnel: It is registered if an ENT-doctor in training (resident) or fellow has operated along with the specialist.
- Surgical time: Surgery time is recorded in minutes for each surgery and described.
- Revision surgery during follow-up: the information and observations as gathered by the surgical report will be collected from all revision surgeries performed during the follow-up of this study.
- **Complications**

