  - Caused by the cholesteatoma (e.g. labyrinth fistula, dura defect, meningoencephalocele, dehiscence of facial nerve, interrupted bony tegmen plate, etc.).
  - Complications during or after surgery (e.g. wound infection, bleeding, damage to the inner ear (resulting in perceptive hearing loss or dizziness), damage to the facial nerve causing facial paralysis, damage to the taste nerve resulting in change in taste, intracranial complications (damage to the tegmen, liquor leakage), tinnitus).
  - Complications that occur within the first 6 weeks after surgery will be registered
- **Quality of life:** Is quality of life comparable between the two techniques? This will be measured using a validated patient reported outcome measure (PROM) in the form of an otological questionnaire (OQUA) and two generic quality of life questionnaires before and after the surgery (27).
  - **OQUA:** This is a otological questionnaire and includes 34 questions, covering eight major types of ear complaints (earache, pressure in the ear, hearing loss, tinnitus, otorrhoea, itch, dizziness, and loss of taste). It measures the frequency and severity of these ear complaints and the impact on quality of life.
  - **EQ5D-5L and HUI3:** The utility scores will be measured to be able to conduct an economic evaluation as described below.
- **Economic evaluation:** A cost-utility analysis will be performed according to the Dutch guideline for economic evaluations in healthcare. Differences with the Belgian guideline for economic evaluations, such the perspective, will be accounted for in the scenario analyses. For instance, in the base case, we will perform the analysis using a societal perspective. In the scenario analysis, we will include a healthcare perspective based on the Dutch base case analysis,

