### 7.2.2 Serious adverse events (SAEs)

A serious adverse event is any untoward medical occurrence or effect that

- results in death;
- is life threatening (at the time of the event);
- requires hospitalisation or prolongation of existing inpatients' hospitalisation;
- results in persistent or significant disability or incapacity; or
- any other important medical event that did not result in any of the outcomes listed above due to medical or surgical intervention but could have been based upon appropriate judgement by the investigator.

An elective hospital admission will **not** be considered as a serious adverse event.

**This study is expected to pose a negligible risk for patients; any SAEs occurring during the study period are expected to be related to the standard treatment and not to the study intervention.** SAE's which could occur as a result of the operation and are always discussed with the patient beforehand as part of standard care are: damage to the inner ear (resulting in perceptive hearing loss or dizziness), damage to the facial nerve causing facial paralysis, intracranial complications. These will only be reported if they occur during or within the first six weeks after surgery as a later onset cannot be seen as a consequence of the intervention.

The investigator will report all SAEs to the sponsor without undue delay after obtaining knowledge of the events. The investigator reports this to the principal investigator and coordinating investigator of the sponsor (UMC Utrecht) per secured e-mail. The sponsor

will report the SAEs through the web portal *ToetsingOnline* to the accredited METC that approved the protocol, within 7 days of first knowledge for SAEs that result in death or are life threatening followed by a period of maximum of 8 days to complete the initial preliminary report. All other SAEs will be reported within a period of maximum 15 days after the sponsor has first knowledge of the serious adverse events.

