### **9.3 Benefits and risks assessment, group relatedness**

The canal wall up procedure with or without obliteration is part of the (inter)national standard care of patients with cholesteatoma. The choice of technique depends largely on the preference and experience of the surgeon. In the literature the obliteration technique is described to result in good hygienic outcomes, the benefit is however not clearly defined. The participating patients in this study are not exposed to any additional risks or harms due to these interventions. Therefore the risk of this research can be considered negligible.

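### Surgical complications, operating time and revision surgery are classed as baseline variables and only described, so the protocol plans no between-arm estimate of early surgical complications, SAEs or operating time

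*Protocol*

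**What the plan says.** Protocol Section 8.2 has a block headed "Baseline variables (patient characteristics, complications, surgical characteristics". The whole plan for that block is: "Will be described using simple descriptive statistics", meaning means or medians with a measure of spread, and frequencies for categories. It names no effect measure or interval and does not say whether the summaries are by arm.

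Section 6.1.2 shows what falls under the heading:

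- Its own baseline list holds demographics, comorbidities and lifestyle, and previous ear surgery. Complications and operating time are not in it.
- Surgical characteristics include operating time ("Surgery time is recorded in minutes for each surgery and described") and revision operations during follow-up.
- Complications come in two kinds: those caused by the cholesteatoma, and "Complications during or after surgery", registered up to 6 weeks after the operation.

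Section 2 lists among the secondary objectives: "Comparing any differences in patient and surgical characteristics". Section 6.2 and Table 1 place randomisation after consent and before surgery.

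**The concern.** A baseline variable is one that the allocated treatment cannot have changed. Wound infection, bleeding, facial nerve damage, minutes in theatre and a later revision operation all arise after randomisation and may depend on whether the mastoid was obliterated. Treating them as baseline puts them in the table that describes who entered the trial, when they belong with what the treatment did. The single word complications also covers disease damage found at surgery and damage done by surgery, so the two could be tabulated together.

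The results will inform whether obliteration is adopted. The benefit, recidivism, gets a relative risk, a risk difference and 95% intervals (Section 8.1). Early surgical complications get counts at most. Bare counts of infrequent events are easily read as no difference in complications when the data cannot exclude an important one.

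**Working it through.** **1. Timing and planned analysis, set side by side**

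| Item | When it arises | Planned analysis |
|---|---|---|
| Patient characteristics | Before randomisation | Descriptive (8.2) |
| Complications caused by the cholesteatoma | Disease process, not the allocated treatment | Descriptive (8.2) |
| Complications of surgery, to 6 weeks | After randomisation | Descriptive, as baseline (8.2) |
| Operating time | After randomisation | Descriptive, as baseline (8.2); also a costing input (6.1.2) |
| Revision surgery in follow-up | After randomisation | Descriptive, as baseline (8.2); confirmed recidivism is analysed in 8.1 |
| Hearing | After randomisation | Between-arm repeated-measures model, inference at 12 months (8.2) |
| OQUA | After randomisation | Between-arm repeated-measures model at 12 and 36 months, inference at 36 (8.2) |

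The first two rows are correctly placed. The next three are not. The serious events that Section 7.2.2 names (inner-ear damage, facial paralysis, intracranial complications) are also in the complications list of Section 6.1.2, so they too fall under the baseline heading. Section 8 gives no other analysis of SAEs.

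**2. Sample size available**

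Section 4.4 states 80 per arm for 20% v 40%, with power 0.8009 and actual alpha 0.0472. Exact enumeration of the two-sided pooled Z test at 80 per arm gives power 0.8009, and alpha 0.0472 at a common rate of 0.40. Both agree. With 10% dropout, 160 / 0.9 = 177.8, so 178, or 89 per arm. Section 4.1 gives a different total (132). I use 178, which follows from the calculation.

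**3. Precision of a complication risk difference**

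The documents give no complication rate, so a common rate p from 2% to 20% is assumed. The 95% half-width is 1.96 × √(2p(1−p)/n). For example, with p = 0.05 and n = 80 it is 1.96 × √(0.095/80) = 0.068.

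| Assumed rate | 80 per arm | 89 per arm |
|---|---|---|
| 2% | ±4.3 points | ±4.1 points |
| 5% | ±6.8 | ±6.4 |
| 10% | ±9.3 | ±8.8 |
| 20% | ±12.4 | ±11.8 |

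Operating time: the half-width is 1.96 × √(2/n) SD, or 0.31 SD with 80 per arm and 0.29 SD with 89.

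**4. Illustrative counts, 89 per arm (Newcombe 95% intervals)**

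- 9 v 2 patients: 10.1% − 2.2% = 7.9 points (0.6 to 16.0).
- 6 v 4 patients: 6.7% − 4.5% = 2.2 points (−5.2 to 9.9).
- 0 of 89 in one arm: upper 97.5% limit 1 − 0.025^(1/89) = 4.1%.

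**5. Why an interval and not a test**

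At 80 per arm, power is about 22% for 5% v 10% and 42% for 10% v 20%. A non-significant test would say little, whereas an interval shows what has not been excluded.

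**The case against.** **Harm is already compared between arms.** The mechanism that the Introduction names, hearing loss after part of the ossicular chain is removed, is covered by the hearing model. The OQUA covers hearing loss, tinnitus, dizziness and taste. This stands, and a reader who infers that the trial has no between-arm estimate of harm at all would be wrong. It does not close the gap. Infection, bleeding, facial paralysis and intracranial events are not OQUA complaints. The OQUA is modelled only at 12 and 36 months, although it is also collected at 6-18 weeks, whereas complications are registered up to week 6.

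**Operating time is not lost.** Section 6.1.2 builds unit costs from surgery duration and plans deterministic and probabilistic sensitivity analyses. This stands too: the cost analysis does not ignore theatre time. What is missing is a clinical between-arm difference in minutes.

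**Descriptive reporting of rare harms is common, and layout belongs in an SAP.** In part. The choice of interval method can be left to an SAP. Here, however, the protocol states a classification and a method, and an SAP written to it would inherit both. Summaries may turn out to be by arm, and a reader could then derive intervals from counts, but Section 8.2 does not say so.

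**The objective in Section 2 is loosely worded.** True. It does not mention complications, and a by-arm table could serve part of it. It does cover surgical characteristics, which include operating time.

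**The safety sections.** A reader might infer that causality is presumed away from Section 7.2.2 ("any SAEs occurring during the study period are expected to be related to the standard treatment and not to the study intervention") and Section 9.3 ("The participating patients in this study are not exposed to any additional risks or harms due to these interventions"). The documents do not support that. The first states an expectation, and the same section still requires the investigator to report every SAE to the sponsor. The second rests on both techniques being standard care. Neither prevents tabulation by arm.

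**The example counts are invented.** Yes. They also sit near an edge: 8 v 2 gives −0.3 to 14.7 points, and Fisher's exact p for 9 v 2 is 0.057. They illustrate width, not an expected result.

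**Conclusion.** The concern holds for a defined set of variables. Complications of surgery, operating time and revision surgery are misclassified as baseline and have a descriptive-only plan, and disease-caused and surgery-caused complications are merged under one word. The protocol therefore plans no between-arm estimate of early surgical complications, SAEs or operating time, which sits badly with its own objective of comparing surgical characteristics. Hearing, OQUA complaints and the costing of surgery time are outside the finding.

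No stated figure is wrong. The size of the issue is the uncertainty that would go unreported: about ±4 to ±12 percentage points on a complication risk difference for assumed rates of 2% to 20%, and about 0.3 SD on operating time. These rest on 80 to 89 patients per arm and on assumed rates, since the documents give none. The recidivism analysis is unaffected.

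**What to change.** Split the Section 8.2 heading.

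- **Baseline, descriptive only:** patient characteristics and complications caused by the cholesteatoma.
- **Outcomes, by allocated arm:** patients with at least one complication of surgery, with at least one SAE, and with any revision operation, each with a risk difference and 95% CI (Newcombe, or exact when events are sparse); operating time as a centre-adjusted mean difference with 95% CI.

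Make no significance claims for these. Section 7.2.2 needs no change.

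The cost is a few lines of protocol or SAP wording and one extra table, from data already planned for collection. The drawback is that intervals for rare events will be wide, and the report should say so.

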## **Economic evaluation**

- A cost utility analysis will be performed as described under the methods section.

The amount of missing data will be mentioned in the results. Missing data will be imputed using multiple imputation. All analyses will be performed on an intention-to-treat basis.

Additionally, dropout rates will be monitored, and any differential attrition between treatment arms will be appropriately accounted for in the statistical analysis.

### **8.3 Interim analysis (if applicable)**

Interim analysis is not deemed necessary, as the study population is not exposed to a considerable increased risk or experimental jeopardizing exposure.

## **9. ETHICAL CONSIDERATIONS**

### **9.1 Regulation statement**

The study will be conducted according to the principles of the Declaration of Helsinki (version 2024, <https://www.wma.net/policies-post/wma-declaration-of-helsinki/>) and in accordance with the Medical Research Involving Human Subjects Act (WMO). The Belgian Center (UZ Leuven) will comply to their own local rules and regulations which may or may not differ from those stated by the WMO.

### **9.2 Recruitment and consent**

Screening for in- and exclusion criteria will be performed by the treating physician. Potentially eligible patients who will undergo a canal wall up surgery for a cholesteatoma will be informed about the study by the treating physician. The treating physician will provide oral and written information (in the form of the information letter including informed consent form) about the study and can when necessary give answers to content-related questions (for example about the surgery). The treating physician will ask the patient if their contact details (name, e-mail address and phone number) may be shared with the study-team member. If the patient gives consent, the treating physician will provide the study-team member with the contact details of the patient.

A trained study-team member will contact the patient for informed consent after a reasonable consideration of at least one day or as much time as needed. The patient has the opportunity to ask questions during this period and during this contact moment. Once all questions have been satisfactorily answered, the patient will be asked to sign the consent form previously given to them by the treating physician or study-team member and return it per post to the department of ENT-surgery of the local hospital (with a return envelope). The trained study-team member will sign the informed consent form as well and return one copy to the patient and keep the original informed consent form for administration. The original informed consent form is stored in a designated folder in a secure location at the local hospital.

After informed consent, the patient will be included in the study and assigned a study number by the researcher and randomly allocated to either group A or B. Participation will be registered in the electronic patient dossier. If the patient does not want to participate, contact with the study-member (not the treating physician) will be terminated. If the patient decides at a later point, after signing the informed consent form or during the study, that they want to stop participation, then the at that point collected data will not be deleted as this would introduce a significant bias into our database. It will also be recorded when patients have declined participation by the treating physician to avoid that the patient is approached again for participation or questions.

### **9.3 Benefits and risks assessment, group relatedness**

The canal wall up procedure with or without obliteration is part of the (inter)national standard care of patients with cholesteatoma. The choice of technique depends largely on the preference and experience of the surgeon. In the literature the obliteration technique is described to result in good hygienic outcomes, the benefit is however not clearly defined. The participating patients in this study are not exposed to any additional risks or harms due to these interventions. Therefore the risk of this research can be considered negligible.

### **9.4 Compensation for injury**

The sponsor/investigator has a liability insurance which is in accordance with article 7 of the WMO. The sponsor (also) has an insurance which is in accordance with the legal requirements in the Netherlands (Article 7 WMO). This insurance provides cover for damage to research subjects through injury or death caused by the study. The insurance applies to the damage that becomes apparent during the study or within 4 years after the end of the study.

## **10. ADMINISTRATIVE ASPECTS, MONITORING AND PUBLICATION**

### **10.1 Handling and storage of data and documents**

Data handling and protection is conducted according to applicable laws and regulations (i.e. GCP, 21 CFR Part 11, GDPR, and ISO 27001, 9001 compliant standards). Confidentiality will be maintained at all times, participant information will not be disclosed to third parties. Once the informed consent is signed by both parties according to the steps described in 9.2, each patient will receive a unique study number to protect their privacy. The original informed consent form will be stored at the local department in a lockable cupboard and a copy will be added to the research file of the patient in Castor. The key to the patient's personal data (name and patient ID) will be safeguarded by the investigator, who is the only one with access to the source data. Every centrum will register their own results in Castor EDC with access control, so that only persons specifically mentioned in the informed consent form have access to the data. All data will be collected using an electronic data capture tool (Castor EDC, a GCP-compliant database). Castor EDC features build in data trails, skips and validation checks. The healthcare data of patient related specifications, CT and DW-MRI images, and any other data as specified in section 6 (Methods) will be derived from the electronic health record. Radiographic scans from PACS are made available for research via our Research Imaging Architecture (RIA). The clinical database will be supplemented with the outcome of a validated questionnaire (the OQUA questionnaire, please see paragraph 3) which will be automatically sent via an email url-link via Castor at set times. The e-mail address (used for questionnaires) will be entered into Castor in an encrypted way and only retraceable to the centre of origin of the patient. Only the team of investigators will have access to the database files in Castor. All generated (meta)data will be stored in a secure research folder structure for access control in each separate participating centre, with only pseudonymized data leaving their centre of origin. To be able to reproduce the study findings and to help future users to understand and reuse the data, all changes made to the raw data and all steps taken in the analysis will be documented in text document. The database file will be kept for 15 years after the study has ended. More details can be found in the Data Management Plan (<https://dmponline.dcc.ac.uk/plans/142594>).
